### Sample size prediction/statistics

It has been shown that the annual event rate for the defined primary endpoint is 6.3% in case of a pathological and 1.0% in case of a normal CMR examination [27]. Retrospective analysis of our data revealed a 30% rate of pathological CMR examinations during the last years, thus the expected annual event rate would be 2.59% for the whole primary CMR group. In patients primarily undergoing coronary angiography, pooled annual event rates have been shown to be about 6% [6, 28]. For the sample size prediction, a Fisher’s exact test with a power of 80% and a *p* value indicating significance of < .05 was used. The study was designed to prove non-inferiority with a defined non-inferiority margin of 1% within a 3-year follow-up period. This lead to a predicted sample size of 90 participants per group. Taking dropout rate and safety margin into account, we plan to enroll 100 patients into each group. Annual interim analyses will be performed to evaluate the need for further enrollment in case of insufficient event rates for an appropriate statistical analysis.

The following statistical tests will be used after completion of follow-up: to test the relationship between categorical classification factors, the chi-squared test will be applied. Continuous variables will be tested for normal distribution by the D’Agostino-Pearson test. In case of a normal distribution, variables will be reported as mean ± standard deviation and a two-tailed *t* test will be applied for comparison. Variables without normal distribution will be reported as median with percentiles and the Mann-Whitney rank-sum test will be used for comparison. As mentioned above, Fisher’s exact test will be applied to test for non-inferiority of the event rates of both groups. Overall, a *p* value ≤ .05 will be judged significant.

Data management will only be carried out by trained personal. The database is stored on protected servers of the academic hospital.

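### Fisher's exact test, as described, does not use the 1% margin: a non-significant result cannot show non-inferiority, and only significant superiority of CMR would imply it

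*Protocol article*

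**What the plan says.** All the relevant text is in the protocol article, Methods/design, Sample size prediction/statistics.

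- Aim and margin: "The study was designed to prove non-inferiority with a defined non-inferiority margin of 1% within a 3-year follow-up period".
- Planning: Fisher's "exact test with a power of 80" per cent and a p "value indicating significance of < .05 was used", giving 90 per group, raised to 100 for dropout and a safety margin.
- Planning rates: "the expected annual event rate would be 2.59% for the whole primary CMR group"; for angiography, "pooled annual event rates have been shown to be about 6" per cent.
- Final analysis: Fisher's "exact test will be applied to test for non-inferiority of the event rates of both groups". The general rule is a p "value ≤ .05 will be judged significant".

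The margin appears only in the sample-size paragraph. The sentence on the final test gives no shifted null hypothesis and no confidence limit to set against 1%, and it does not say whether Fisher's test is one-sided or two-sided. Whether the 1% is an absolute difference in 3-year risk is not spelled out either; that reading is used below.

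**The concern.** Non-inferiority is the trial's stated objective in the abstract, the Background and the Discussion. The hypothesis to reject is that the CMR risk exceeds the angiography risk by the margin or more. Fisher's exact test in its standard form rejects, or fails to reject, equality of the two risks, which is a different question. The article names both the test and its purpose, and they do not match.

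What is at stake is how the p value will be turned into a conclusion. If a non-significant p is taken as support for non-inferiority, there is almost no protection against a false claim. If a significant p favouring CMR is required, the trial is in effect a superiority trial and will miss non-inferiority that its data could show. The article does not say which applies. The trial is open-label, and its investigators adjudicate endpoints and run the interim analyses, so the choice should not be left until data are in hand.

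**Working it through.** **1. Planning rates.** CMR: 0.30 × 6.3% + 0.70 × 1.0% = 2.59% per year, which reproduces the article. Over 3 years:
- CMR: 3 × 2.59% = 7.77% (linear) or 1 − (1 − 0.0259)³ = 7.57% (compound).
- Angiography: 3 × 6% = 18% (linear) or 1 − 0.94³ = 16.94% (compound).

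**2. The stated 90 per group.** It does not reproduce from the stated inputs. Exact Fisher power for equality, linear rates, reaches 80% at about 146 per group (one-sided) or 184 (two-sided). At 90 per group it is 59% or 47%. This is a related but separate problem.

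**3. Non-significant is not non-inferior.** Take 18 CMR and 12 angiography events, 100 patients each. Two-sided Fisher p = 0.32. The Wilson 95% limits are 11.7% to 26.7% for 18/100 and 7.0% to 19.8% for 12/100. Newcombe's interval for the difference (CMR minus angiography) is then:
- upper: 0.06 + √[(0.267 − 0.18)² + (0.12 − 0.070)²] = +16.0 points
- lower: 0.06 − √[(0.18 − 0.117)² + (0.198 − 0.12)²] = −4.0 points

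The data are compatible with an excess of 16 times the margin.

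**4. Long-run behaviour if non-significance were accepted** (two-sided Fisher, 100 per arm, binomial probabilities summed over all tables):

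| True 3-year risk, CMR vs angiography | Not significantly worse |
|---|---|
| 8.57% vs 7.57% (exactly at the margin) | 97.5% |
| 12.57% vs 7.57% | 84.6% |
| 15.14% vs 7.57% | 68.3% |

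A rule comparing a two-sided 95% limit with the margin has a nominal false-claim rate of 2.5% in the first row.

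**5. A significant result favouring CMR does imply non-inferiority.** With 7 CMR and 17 angiography events, p = 0.048 and the Newcombe interval is −19.3 to −0.9 points, wholly below +1. Of all 441 tables with up to 40 events per arm and p ≤ .05 favouring CMR, none had an upper Newcombe limit at or above +1 point.

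**6. But requiring it is too strict.** With 8 CMR and 18 angiography events, close to what the linear rates predict, p = 0.057, so Fisher fails; the Newcombe interval is −19.5 to −0.6 points, which excludes a 1-point excess. In the same range of tables, 59 of 799 non-significant ones had an upper limit below +1 point. Chance of success at 100 per arm under the plan's rates:

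| Rule | Compound | Linear |
|---|---|---|
| Fisher two-sided, p ≤ .05 favouring CMR | 45% | 51% |
| Upper limit of 95% CI below +1 point, Newcombe | 61% | – |
| Upper limit of 95% CI below +1 point, Wald | 63% | 68% |

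If one-sided 0.05 was meant, Fisher gives 58% (compound) or 64% (linear), and the matching Wald bound 74% or 79%. The gap is of similar size.

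**7. Sample size for the margin-based rule.** n = (1.960 + 0.842)² × [p_C(1 − p_C) + p_A(1 − p_A)] / (0.01 + p_A − p_C)², at 80% power:
- linear: 7.85 × (0.0717 + 0.1476) / 0.1123² ≈ 137 per group
- compound: 7.85 × (0.0700 + 0.1407) / 0.1037² ≈ 154 per group

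**The case against.** Several arguments limit this point.

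*A significant result does answer the question in one direction.* A reader might infer that the test is meaningless whichever way it comes out. The text does not support that. Significant superiority of CMR excludes a 1-point excess (step 5), and it is the direction the planning rates assume. This stands.

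*The article never says that non-significance will count as non-inferiority.* Correct. The rates in step 4 describe what would happen under that reading, not what the investigators have committed to. They show why the reading must be ruled out.

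*Poor performance at equal rates is not mainly Fisher's doing.* With equal true rates and 100 per arm, Fisher favours CMR significantly in only 1.3% to 1.7% of trials, which a reader might charge to the test. The margin-based rule succeeds only about 4% of the time there. The limit is a 1-point margin with 100 per arm.

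*Incomplete follow-up.* A reader might infer from the dropout allowance that such patients must be discarded or counted as event-free. The article does not say so. Follow-up is a fixed 3 years per patient, so comparing 3-year proportions is legitimate, and the handling of missing follow-up is commonly left to the analysis plan.

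*An analysis plan that is not shown could specify a margin-shifted test.* It could. But the article names Fisher's exact test for this purpose, so this is a stated mismatch and not a gap left for another document.

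**Conclusion.** The point holds in a limited form. The named primary test addresses equality and does not use the margin. When non-significant it says nothing reliable about non-inferiority; when significantly in favour of CMR it implies non-inferiority, but at a needless cost of about 16 percentage points of success probability (45% against 61%, compound rates, 100 per arm).

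These figures assume 3-year risks derived from the article's annual rates, independent binomial counts, complete follow-up, a two-sided Fisher test and a margin of 1 absolute percentage point over 3 years. Another scale for the margin would change the size but not the defect, because Fisher's test as described uses no margin at all. The trial's main conclusion depends on this rule, so it should be corrected before any analysis.

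**What to change.** Replace the sentence on Fisher's exact test with a paragraph that:

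1. states the null hypothesis: 3-year risk under CMR minus 3-year risk under angiography is at least the margin;
2. states the scale and time frame of the margin, and the alpha with its sidedness;
3. concludes non-inferiority only if the upper limit of the two-sided 95% confidence interval for the risk difference lies below the margin, naming one method (for example Miettinen-Nurminen, Farrington-Manning or Newcombe);
4. says that a non-significant difference will not be reported as non-inferiority.

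Restate the power for this rule: about 61% to 68% at 100 per group under the plan's own rates. Restoring 80% would take about 137 to 154 per group under the same rates.

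The cost is one paragraph and a less favourable stated power. The change does not help if the two strategies truly have equal risk. With a 1-point margin and equal 3-year risks assumed at 7.8% to 18%, about 8,900 (7.8%, one-sided 0.05) to 23,200 (18%, one-sided 0.025) patients per group would be needed. The paragraph should say so plainly.

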## Discussion

In contrast to the recommendations given in current guidelines, diagnostic coronary angiography remains the most often applied modality in the evaluation of patients with stable CAD [1, 2]. In consequence, a high rate of angiographies without detection of obstructive CAD results [13, 15]. This is of special interest, as there is a remarkable frequency of complications associated with this procedure [15]. On the other hand, many diagnostic angiographies are followed by interventional revascularization procedures without prior functional assessment of visually detected coronary stenosis [16]. Taken together, expansion of invasive diagnostic and therapeutic procedures lead to a growing economic burden stressing health care systems without evidence for ameliorated patient care [6].

CMR is an important diagnostic modality in the growing arsenal of cardiology. Its ability to reliably and simultaneously evaluate global cardiac function and myocardial ischemia has been proven previously [11]. In particular, the high negative predictive value of a normal CMR examination with regard to the occurrence of major cardiac endpoints predisposes this modality to act as gatekeeper prior to revascularization strategies [29].

To the best of our knowledge, there is only one study prospectively randomizing patients to a CMR-driven versus an angiography-driven management strategy [12]: the MR-INFORM trial was a randomized multicenter study comparing a FFR- versus a CMR-based management approach of stable CAD patients. Non-inferiority of the CMR-based strategy could be demonstrated within a 12-month follow-up. In the present trial, a follow-up for up to 3 years is planned for every patient, thus providing information on long-term outcomes for each management strategy. Moreover, besides major clinical endpoints, symptom burden and quality of life will also be assessed. This is of special interest since clinical decision-making always should be based on patient comfort and satisfaction.

If the present study can accomplish its aim to prove non-inferiority of the CMR-based approach in the management of patients with stable CAD, its importance may further increase. This might result in a reduction of adverse events associated with coronary angiographies and revascularization procedures. This trial, therefore, aims to contribute important evidence with regard to the management of stable CAD patients.

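### The primary non-inferiority test on crude 3-year event proportions cannot use partial follow-up, although the plan expects dropout

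*Protocol article*

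**What the plan says.** All of the following is in the protocol article.

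- **Primary test** (Sample size prediction/statistics): Fisher's "exact test will be applied to test for non-inferiority of the event rates of both groups". The same test underlies the sample size: an "exact test with a power of 80"% and a p "value indicating significance of < .05 was used". The other tests listed are chi-squared, t and Mann-Whitney. No time-to-event method appears.
- **Margin** (same section): a "defined non-inferiority margin of 1% within a 3-year follow-up period".
- **Assumed rates** (same section): for angiography, "pooled annual event rates have been shown to be about 6"%; for CMR, "the expected annual event rate would be 2.59% for the whole primary CMR group".
- **Dropout** (same section): 90 per group is raised to 100: "Taking dropout rate and safety margin into account, we plan to enroll 100 patients into each group". No rate is given, overall or by group.
- **Follow-up** (Follow-up section): three years for each patient, with yearly clinic visits and telephone contact with patients and their general practitioners. If consent is withdrawn, data already collected are taken out of the analysis. Nothing is said about patients lost without withdrawing consent.

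**The concern.** Fisher's test works on a table of patients with and without an event at 3 years. A patient last seen event-free at 14 months fits neither cell. Any counting rule has to assign that patient an outcome or drop the patient, and neither makes proper use of the 14 months observed.

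Counting such patients as event-free lowers a group's apparent risk. Dropping only the event-free lost, while keeping those who had an event first, raises it. If the groups lose patients at different rates, the two distortions do not cancel. The trial is open-label and one group has no initial angiography unless ischaemia is found, so unequal loss is possible. If the CMR group lost more patients and they were counted as event-free, the shift would favour non-inferiority.

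This is separate from whether Fisher's test can accommodate a margin at all. A margin-based test on the same crude proportions would share the weakness.

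**Working it through.** **The plan's own figures.** The CMR rate reproduces: 0.3 × 6.3% + 0.7 × 1.0% = 2.59% a year. So does the enrolment step: 90/(1 - 0.10) = 100, which allows at most 10% loss, including an unspecified safety margin. I take 90 as stated; whether it follows from the design inputs is another question.

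**Assumptions (not in the article).** Constant event hazard; dropout at a constant hazard, independent of events; no non-cardiac deaths; the margin read as 1 percentage point over 3 years. Dropout d is the 3-year probability of being lost if no event intervened. The values of d are mine.

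**Formulas.** With annual rate r:
- event hazard λ = -ln(1 - r); dropout hazard μ = -ln(1 - d)/3
- true 3-year risk = 1 - (1 - r)³
- observed events E = λ/(λ + μ) × [1 - exp(-3(λ + μ))]
- crude risk, lost counted as event-free: E
- crude risk, event-free lost excluded: E/[E + (1 - r)³(1 - d)]

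**Example, r = 6%, d = 5%.** λ = 0.0619, μ = 0.0171, (0.94)³ × 0.95 = 0.7891. E = 0.7835 × 0.2109 = 16.53%. Excluding the event-free lost: 0.1653/(0.1653 + 0.7891) = 17.32%.

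| Annual rate | True 3-year risk | d | Lost = event-free | Event-free lost excluded |
|---|---|---|---|---|
| 6% | 16.94% | 5% | 16.53% | 17.32% |
| 6% | 16.94% | 10% | 16.11% | 17.73% |
| 6% | 16.94% | 15% | 15.68% | 18.17% |
| 2.59% | 7.57% | 5% | 7.38% | 7.76% |
| 2.59% | 7.57% | 10% | 7.19% | 7.96% |
| 2.59% | 7.57% | 15% | 6.99% | 8.18% |

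**Spurious difference, CMR minus angiography, equal true risks.**
- 6% a year, dropout 5% (angiography) v 15% (CMR): 15.68 - 16.53 = -0.85; 18.17 - 17.32 = +0.85 points
- 6% a year, 5% v 10%: 16.11 - 16.53 = -0.42; 17.73 - 17.32 = +0.41
- 2.59% a year, 5% v 15%: 6.99 - 7.38 = -0.39; 8.18 - 7.76 = +0.42
- equal dropout: 0 in every case

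**Timing of dropout.** Uniform dropout times give -0.82/+0.88 for the first case. If everyone lost leaves at the start, it is 16.94 × (0.85 - 0.95) = -1.69 when counted as event-free, and 0 when excluded.

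**With censoring instead.** Under the same independent dropout, a 3-year cumulative-incidence estimate with censoring at last contact has an expected difference of 0 for any dropout split.

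**Against sampling error.** The standard error at 16.94% risk is √(2 × 0.1694 × 0.8306/n): 5.6 points at n = 90 and 5.3 at n = 100. So 0.85 points is about 0.15 to 0.16 standard errors. At the margin this lifts a one-sided 5% error to about 6.8%: Φ(-1.645 + 0.152) = 0.068 at n = 90.

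**At the design rates.** The true difference is 7.57 - 16.94 = -9.37 points. With a 5%/15% split in either direction, the table gives between 7.38 - 15.68 = -8.30 and 7.76 - 18.17 = -10.41. If all dropout is at the start, the least favourable split gives 7.57 × 0.95 - 16.94 × 0.85 = -7.21.

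**The case against.** **No counting rule is stated, and such detail is usually left to the SAP.** This stands against a reader who infers that the plan miscounts lost patients: it does not say how they are counted. It does not remove the point. The article fixes the test, and whatever rule an SAP adds must still put each lost patient in a cell or leave the patient out.

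**The one stated rule behaves differently.** Withdrawal of consent removes all of a patient's data. Under independent withdrawal, complete removal leaves a non-fatal endpoint unbiased (16.94% in both groups at 5% v 15%). Because patients who have died cannot withdraw, about 0.2 points would remain if a quarter of events were fatal and about 0.4 if half were. So the +0.85 figure does not describe this rule; it applies to excluding only the event-free lost. The rule does not cover patients lost without withdrawing.

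**Fixed follow-up makes a binary 3-year endpoint legitimate.** True with complete data, and general practitioners may supply some missing outcomes. A reader might take "a follow-up for up to 3 years is planned for every patient" in the Discussion as a sign of variable follow-up, but the Follow-up section plans three years for each patient. The point rests on the expected dropout alone.

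**Non-cardiac deaths.** A reader might add that counting a non-cardiac death as event-free makes the risk too low. It does not: that patient can never have the primary event, and cumulative incidence with a competing event treats the patient in the same way. The point is confined to patients lost to follow-up.

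**The dropout gap is assumed and its effect is small.** Both are correct, and they limit the verdict.

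**Conclusion.** The point holds in limited form. The article fixes a primary test that cannot use partial follow-up, in a plan that expects dropout, and a better method is readily available.

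The size is illustrative. With a 10-point dropout gap at 6% a year in both groups, the spurious difference is about 0.85 points in either direction, against a stated 1% margin. With a 5-point gap, or at 2.59% a year, it is about 0.4. With equal dropout and equal risks it is nil. If 1% was meant per year (3 points over 3 years), 0.85 is about 28% of the margin.

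A reader might infer that dropout will use up most of the margin, or that the trial's conclusion will turn on how lost patients are counted. The documents support neither. They give no dropout by group, the shift is under one patient per 100 and about 0.15 standard errors, and it would not change the result at the design rates. It matters only if the estimate falls near the margin. The change is worth making because it is cheap and removes a discretionary choice, not because the present test would be decisively wrong.

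**What to change.** Make the primary analysis the 3-year cumulative incidence of cardiac death or non-fatal infarction in each randomised group. Use the Aalen-Johansen estimator, with non-cardiac death as a competing event and patients lost to follow-up censored at last contact. Report the risk difference, CMR minus angiography, with its confidence interval. Declare non-inferiority only if the upper limit lies below the stated margin.

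The cost is analysis-plan wording. Event and last-contact dates should be available from the yearly follow-up. The method assumes that censoring is non-informative, so add one sensitivity analysis for lost patients. Patients whose data are deleted on withdrawal of consent stay outside the analysis whichever estimator is used; report their number by group.

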## Discussion

In contrast to the recommendations given in current guidelines, diagnostic coronary angiography remains the most often applied modality in the evaluation of patients with stable CAD [1, 2]. In consequence, a high rate of angiographies without detection of obstructive CAD results [13, 15]. This is of special interest, as there is a remarkable frequency of complications associated with this procedure [15]. On the other hand, many diagnostic angiographies are followed by interventional revascularization procedures without prior functional assessment of visually detected coronary stenosis [16]. Taken together, expansion of invasive diagnostic and therapeutic procedures lead to a growing economic burden stressing health care systems without evidence for ameliorated patient care [6].

CMR is an important diagnostic modality in the growing arsenal of cardiology. Its ability to reliably and simultaneously evaluate global cardiac function and myocardial ischemia has been proven previously [11]. In particular, the high negative predictive value of a normal CMR examination with regard to the occurrence of major cardiac endpoints predisposes this modality to act as gatekeeper prior to revascularization strategies [29].

To the best of our knowledge, there is only one study prospectively randomizing patients to a CMR-driven versus an angiography-driven management strategy [12]: the MR-INFORM trial was a randomized multicenter study comparing a FFR- versus a CMR-based management approach of stable CAD patients. Non-inferiority of the CMR-based strategy could be demonstrated within a 12-month follow-up. In the present trial, a follow-up for up to 3 years is planned for every patient, thus providing information on long-term outcomes for each management strategy. Moreover, besides major clinical endpoints, symptom burden and quality of life will also be assessed. This is of special interest since clinical decision-making always should be based on patient comfort and satisfaction.

If the present study can accomplish its aim to prove non-inferiority of the CMR-based approach in the management of patients with stable CAD, its importance may further increase. This might result in a reduction of adverse events associated with coronary angiographies and revascularization procedures. This trial, therefore, aims to contribute important evidence with regard to the management of stable CAD patients.

